## Abstract

**Introduction:**

Psychological disorders including depression and anxiety are significant public health concerns. A Mediterranean-style dietary pattern (MDP) has been associated with improved mental well-being in observational studies. Evidence of the acute (defined as postprandial to 1 week) effects of an MDP on brain function, mood, cognition and important modulators, including sleep and the gut microbiota is limited. The current intervention aims to examine whether an MDP, compared with a Western diet (WD), improves mood, cognition and anxiety symptoms, postprandially, at 24-hour and after 5 days in adults with mild to moderate anxiety and depression.

**Methods and analysis:**

Twenty-five UK adults (aged 18 or over) with mild to moderate anxiety and/or depression and low adherence to an MDP were recruited to a cross-over randomised controlled trial. Each participant undergoes a 5 day MDP and a 5 day WD in a randomised order with all meals provided. The co-primary outcomes are mood and anxiety, with secondary outcomes including cognitive function, brain perfusion (as assessed by MRI), sleep quality, blood pressure, plasma glucose, insulin, lipids, C-reactive protein, cortisol, brain-derived neurotrophic factor, gut microbiota speciation and microbial metabolites including short chain fatty acids. A linear mixed model and/or paired analysis will be used to compare the effects of treatments over time.

**Ethics and dissemination:**

The study has received a favourable ethics opinion from the National Health Service London Queen Square Research Ethics Committee (22/LO/0796). The results will be disseminated through scientific journals and conferences.

**Trial registration number:**

NCT05927376.

STRENGTHS AND LIMITATIONS OF THIS STUDYThe design of MediMood was informed by a systematic review of the literature which provided the need for, and informed the design of, the current randomised controlled trial (RCT).MediMood is a highly controlled efficacy RCT with all food provided for 5 days with detailed food preparation instructions rather than dietary advice only.The study quantified key physiological determinants of brain health including gut microbiota and brain perfusion quantified by MRI.To minimise participant burden, the primary outcomes (mood and anxiety) and biological samples collection could not be conducted daily.For logistical and costs reasons, MRI scans could not be executed at the beginning and at the end of the 5 day interventions, to assess short-term changes in brain perfusion, limiting us to assessing only the postprandial effects of dietary intervention on cerebral blood flow.

## Introduction

 Mental health disorders represent a major public health challenge.^1^ In 2019, depression exceeded 280 million cases globally, and anxiety surpassed 300 million cases, as the two most common forms of mental health disorders.^1^ Mental health disorders have constituted around 15% of ‘years lived with disability’ worldwide since 1990,^2^ with depression predicted to be the global leading cause of disease by 2030.^3^ In England, nearly 20% of adults report depression, anxiety, sleep problems, poor concentration and forgetfulness.^4^

The economic impact of mental health disorders are substantial, with an estimated annual global cost of approximately $5 trillion including loss of productivity.^5^ The UK National Health Services (NHS) has allocated a £2.3 billion budget for the years 2023–2024 for mental health services as part of its long-term plan.^6^

The main treatment for mental health disorders are antidepressant medications and psychotherapy; both can cause negative side effects,^7^ stigma^8^ and have poor uptake.^4^ Despite increased treatment in recent decades, no decrease in the prevalence of mental disorders is evident,^9^ underlining the need for alternative intervention approaches.

The WHO has highlighted the critical need for ‘affordable, effective and feasible strategies to promote, protect and restore mental health’, and launched several initiatives such as the ‘Comprehensive Mental Health Action Plan 2013–2030’^10^ and the ‘World mental health report: transforming mental health for all’^11^ to address these needs.

A Mediterranean-style dietary pattern (MDP) consists of high amounts of fruits, vegetables, legumes, nuts, olive oil and fish. It is low in high fat dairy, red and processed meat, carbonated beverages and free sugars, and rich in unsaturated fatty acids, polyphenols and unrefined complex carbohydrates,^12^ which aligns with healthy eating guidelines in the UK and many other countries.^13^

Long-term adherence to an MDP has been consistently shown to protect mental health. Longitudinal analysis of the SUN cohort (n=10 094) reported that higher MDP adherence was correlated with a lower depression incidence after 4.4 years,^14^ supported by a meta-analysis of observational studies showing a reduced risk of depression associated with long-term MDP adherence (OR=0.72; 95% CI, 0.60 to 0.87).^15^ The Prevencion con Dieta Mediterranea (PREDIMED), the hallmark randomised controlled trial (RCT) in the field, reported a 41% reduction in depression among at-risk individuals with type 2 diabetes who followed an MDP supplemented with nuts for 3 years (HR=0.59; 95% CI, 0.36 to 0.98).^16^ The HELFIMED,^17^ SMILES^18^ and AMMEND^19^ trials, all of which examined the effects of an MDP on depression in adults with moderate to severe depression over the course of 3–6 months, demonstrated significant decrease in depressive symptoms. The cognitive benefits of an MDP have also been consistently reported. The PREDIMED study showed improved cognition after MDP interventions,^20^ while a recent UK Biobank analysis suggested a reduced risk of future dementia associated with MDP consumption.^21^ Additionally, a meta-analysis reported a linear dose–response relationship between an MDP adherence and the risk of future cognitive disorders.^22^

On the other hand, a Western diet (WD), which includes high amounts of saturated fat (SFA) and simple sugars, is associated with compromised brain health, and a higher incidence of depression, anxiety and neurological conditions.^23 24^

Our systematic review investigating the short-term effects (up to 10 days) of an MDP on brain health revealed improved mood and cognition, in particular, alertness, contentment and attention domains in the four included studies.^25^ There were too few studies to draw firm conclusions, and we identified several limitations and research gaps. Three of the four studies were of 10 days duration, with no shorter term or postprandial data available. Besides, in all reviewed studies, participants were provided with dietary advice rather than the intervention diet, and adherence to the intervention was not monitored. Furthermore, mental health outcomes were not comprehensively assessed to elucidate which domains are most responsive to a short-term MDP intervention and little attention has been given to possible underlying mechanisms which could be mediating the acute effects of an MDP such as changes in inflammation, glucose regulation, cerebral blood flow (CBF) and the gut microbiota.^25^

Therefore, despite its potential benefits^25^ on mental well-being and quality of life, the acute effects of an MDP are largely unknown. The overall aim of MediMood study is to examine the impact of an MDP versus a Western-style diet (WD) on mood, anxiety and cognition postprandially, at 24-hour (mood and anxiety only) and after 5 days, and to investigate underpinning physiological mechanisms.

## Methods and analysis

This article follows the Standard Protocol Items: Recommendations for Interventional Trials (SPIRIT) guidelines.^26^

### Study setting

MediMood is a single-centre cross-over RCT conducted at the University of East Anglia (UEA), and the NHS Clinical Research Facility (CRF) intervention centre, based at the Quadram Institute (QI), in Norwich, UK. The data collection period spanned from June to December 2023.

### Eligibility criteria

Potential participants were recruited from the general population and from the University staff and students, using advertising posters/leaflets, internal emails and social media.

Twenty-five people aged 18 years or over were recruited. Participants were eligible if they met the following conditions:

Had mild to moderate level depression and/or anxiety, established using the Patient Health Questionnaire (PHQ-9) (score 5-14/27)^27^ and the Generalised Anxiety Disorder (GAD-7) (score 5-14/21).^28^ Both measures are commonly used in the NHS settings as preindicators of depression and anxiety.Were not already following an MDP, established using the Mediterranean Diet Adherence Screener (MEDAS) (score≤7/14) (online supplemental appendix 1).^29^Had been on the same dosage of their medication for at least 3 months and expected to keep a stable dosage for the next 3 months (for those who are on any antidepressant/antianxiety medication).Were eligible to undertake an MRI scan (eg, not having any possibility of pregnancy).Were not vegan or vegetarian.Did not have food allergies or intolerances to the food provided such as fish and nuts.

If participants reported antibiotics use in the last month, their participation was postponed until 1 month after treatment to allow the gut microbiota composition to return to its habitual status. Participants are requested to keep any probiotic supplement use and physical activity levels stable during their participation. For MRI safety, ‘any possibility of being pregnant’ or those with specific medical implants or devices (such as cardiac pacemakers or artificial limbs) were precluded from participating (online supplemental appendix 2, MRI Safety Screening Form). Participants were advised to discuss their participation with their general practitioners (GPs) and informed that the study researchers were going to inform their GPs about their participation (online supplemental appendix 3, Participant Information Sheet).

Table 1 lists the full inclusion and exclusion criteria.

**Table 1 T1:** The eligibility criteria

Inclusion criteria	Exclusion criteria
Males and females aged 18 or over	Vegan, vegetarian
Mild to moderate level anxiety and/or depression (PHQ-9 and/or GAD-7 scores of 5–14)	Allergic to any of the study components for example, nuts and fish
Low MDP adherence (MEDAS score≤7/14)	On antianxiety and/or antidepressant medication which has changed in the last 3 months or likely to change in the next 3 months
Able to have an MRI scan	Unwilling or unable to make changes to their diet for 10 days (2×5 days period)
Computer literate with internet access	Unable to attend the intervention centre
Fluent in written and spoken English	MEDAS score>7
Gave consent for the study team to contact their GP	Not fluent in written and spoken English
Willing and able to comply with all study procedures including diet	MRI unsafety
	Not agreement for the study team to contact their GP
	Not prepared to make changes to diet for 10 days (2×5 days period)

GAD-7Generalised Anxiety Disorder (includes 7-item)GPgeneral practitionerMDPMediterranean-style dietary patternMEDASMediterranean Diet Adherence Screener tool (includes 14-items)PHQ-9Patient Health Questionnaire (includes 9-item)

### Recruitment

Individuals who expressed an interest in the study were provided with the Participant Information Sheet and directed to the study website (https://app.mantal.co.uk/medimood), built on the Mantal platform, an online research management portal. First, participants were asked to provide consent (online supplemental appendix 4, Consent Form). Second, participants completed questionnaires to ascertain if they meet the study inclusion criteria detailed above. Those meeting the criteria were enrolled in the study and randomised to either an MDP or a WD for arm 1 of the study, by using random number generator in Microsoft Excel.

The study stages are displayed in figure 1.

**Figure 1 F1:**
[figure not shown]
Study flow diagram. GAD-7, Generalised Anxiety Disorder (includes 7-item); MEDAS, Mediterranean Diet Adherence Screener; PHQ-9, Patient Health Questionnaire (includes 9-item); WD, Western-style diet.

### Safeguards for maintaining psychological well-being of participants

Enrolled participants’ GPs are notified about their patients’ participation and provided with their PHQ-9 and GAD-7 scores. The GPs of participants who are ineligible due to severe levels of anxiety and/or depression were also notified. All participants are signposted to mental health and well-being support.

### Interventions

The experimental arm is a 5 day MDP, with a 5 day WD comparator arm. Both diets are designed to provide approximately 2000 kcal/day (±10% flexibility per day, ranging between 1800 and 2200 kcal). The MDP diet scores 14 (or 13 if no alcohol is consumed) on the MEDAS scale (maximum score 14) on each of the 5 days. Conversely, the WD scores zero points on the MEDAS scale on each of the 5 days. The full meal plans are presented in the online supplemental appendix 5.

The total macronutrient (carbohydrates, fat and protein) composition, and free sugars, fibre, SFA and monounsaturated fat content of the diets have been designed to ensure that they represent typical MDP and WD. For the MDP, the PREDIMED diet was used as the reference standard^30^ and for the WD, the nutrient profile was based on extreme nutrient intakes (lowest or highest 2.5%) of the UK population using the UK National Diet and Nutrition Survey (NDNS) data (https://www.gov.uk/government/collections/national-diet-and-nutrition). Table 2 represents the nutrient compositions of the test lunch meals, and table 3 represents the nutrient compositions of the full 5 day diets.

**Table 2 T2:** Nutrient composition of the lunch test meals (day 1) taken from the product labels

		Mediterranean diet	Western diet
Energy	Kcal	1013	984
Carbohydrates	g	45	123
	%	18.3	50.3
Free sugars	g	0	83
Fibre	g	10.6	2.9
Proteins	g	60	37.5
	%	24.3	15.3
Total fat	g	63	37.3
	%	57.4	34.4
SFA	g	8.8	15.2
	%	7.8	14

%, contribution to the total daily energy intake as per cent; g, grams; kcal, kilocalories; SFA, saturated fatty acids

**Table 3 T3:** Nutrient composition table of the 5 day test diets

		Mediterranean diet (mean±SD)	Western diet (mean±SD)
Energy	Kcal/day	1878±46	2027±79
Carbohydrates	g/day	154.2±16.2	230.8±24
	%	32.8±3.0	45.5±4.6
Free sugars	g/day	0.3±0.6	35.7±10.4
Fibre	g/day	34.8±6.4	10.6±2.9
Proteins	g/day	80.8±19.1	64.6±11.4
	%	17.1±4	12.7±2.3
Total fat	g/day	105.0±8.9	94.2±11.2
	%	50.3±4.6	41.8±4.6
SFA	g/day	16.1±2.0	37.1±3.9
	%	7.2±1.0	16.5±1.3
MUFA	g/day	43.5±6.1	5.0±2.6
PUFA	g/day	16.9±7.5	2.6±3.0
Omega-3 PUFA	g/day	2.4±1.5	0.7±0.1
Omega-6 PUFA	g/day	9.3±6.6	0.6±0.7

%, contribution to the total daily energy intake as per cent; g, grams; kcal, kilocalorie; MUFA, monounsaturated fatty acids; PUFA, polyunsaturated fatty acidsSFA, saturated fatty acids

To capture their habitual dietary intake prior to the study, the participants are asked to complete the European Prospective Investigation into Cancer and Nutrition study Food Frequency Questionnaire (EPIC FFQ; https://www.epic-norfolk.org.uk/about-epic-norfolk/nutritional-methods/ffq/) before their baseline visit. To promote adherence, all study foods are delivered to participants’ homes using a supermarket delivery service, with extra food provided for the evening meals for one other person at home. Participants are provided with booklets (online supplemental appendix 6), with guidance as to how to store and prepare the meals and which additional foods and snacks can be consumed if hungry. The snacks are chosen to ensure they do not affect the MEDAS score of the study arm. To track dietary compliance, participants are asked to record all foods and beverages on the daily checklists in the booklets and provide notes and feedback. Participants are contacted daily to encourage dietary adherence.^31^

Participants are asked to visit the intervention centre on day 1 (figure 2), from 08:00 until approximately 15:30. Before their arrival, they are required to collect a urine and faecal sample at home using sample collection kit provided at least 2 days prior to their day 1 visits. The kit includes a stool sample catcher, two plastic tubes with scoop, a biohazard bag, a sealable bag, a urine sample collection pot with a sealable bag, a pair of disposable gloves, an insulated cool bag, two freezer blocks with two sterile outer bags and instructions. They are asked to collect the faecal sample within 24 hours prior to their clinical visit, and the urine sample as the first pass on the morning of their visit (day 1). Participants arrive at the intervention centre in a fasted state (fasted from 20:00 the night before). On arrival, anthropometric (weight and height) and blood pressure (BP) measurements are taken. A nurse collects the baseline blood sample. Participants are then provided with a honey and oat cereal bar. After 15 min rest, participants undergo the mood, anxiety, cognition and sleep testing via the study website; 90 min after completing these tests, participants are served either an MDP or a WD test meal (at 11:30) depending on the arm they are randomised to. Following the meal, participants’ BP is measured at 12:45 and start postprandial mood and cognitive testing at 13:00. At 14:00, they undergo the brain MRI scan and provide a postprandial blood sample at 15:15. Afterwards, participants are provided with an afternoon snack before leaving the unit and consume their day 1 dinner at home. On day 2 morning, participants complete online mood and anxiety testing at home after having a honey and oat cereal bar. On days 2–5, participants complete a sleep diary. An actigraphy is worn throughout the intervention period. On completion of the 5 day intervention, participants return to the intervention centre on the morning of day 6 (08:00–10:00) to repeat the morning assessments, as carried out on day 1 (figure 2).

**Figure 2 F2:**
[figure not shown]
The protocol for the intervention centre visits. On the day 1 visit, participants undergo the full protocol. On day 6 visit, participants undergo the morning session only. CBF, cerebral blood flow; MDP, Mediterranean-style dietary pattern; WD, Western diet.

As menstruation-related hormonal fluctuations can cause disturbance in mood,^32^ neurocognitive functions^33^ and sleep,^34^ a wash-out period of 23-days was chosen to ensure female participants are on the same phase of their menstrual cycle on each intervention arm (ie, 28 days between arm 1 day 1 and arm 2 day 1).

### Outcomes

All outcome measures are summarised in table 4.

**Table 4 T4:** Summary of the outcome measures

	Measurement	Tool used	Time point	Time per measurement point	Location
Screening	Mood	PHQ-9	Prebaseline	9 min	Home
	Anxiety	GAD-7	Prebaseline	6 min	Home
	Initial dietary habits	MEDAS	Prebaseline	10 min	Home
During interventions	Initial dietary profile	EPIC FFQ	Baseline	30 min	Home
	Mood and anxiety	Bond-Lader VAS,POMS	Baseline, postprandial, 24 hours,day 6	30 min	Home (24 hours) and intervention centre (baseline, postprandial and day 6)
	Cognitive functions	NeurOn battery	Baseline, postprandial,day 6	30 min	Intervention centre
	CBF	MRI	Postprandial	30 min	UWWBIC
	Blood pressure		Baseline, postprandial,day 6	5 min	Intervention centre
	Blood samples		Baseline (≥10 hour fasting), postprandial,day 6 (≥10 hour fasting)	15 min	Intervention centre
	Urine and faecal samples		Baseline,day 6		Home collection kits are provided
	Weight and height	SECA scale	Baseline,day 6	5 min	Intervention centre
	Initial sleep profile	PSQI	Baseline	10 min	Intervention centre
	Sleep quality	ActigraphyKSDKSS	Over 5 days	Continuously (for actigraphy)5 min (for KSD and KSS)	Home
	Subjective dietary review score	Non-validated single question	Day 6		Intervention centre
Follow-up	Dietary behaviour	MEDAS	3 months	10 min	Home

CBFcerebral blood flowEPIC FFQEuropean Prospective Investigation into Cancer and Nutrition study Food Frequency QuestionnaireGAD-7Generalised Anxiety Disorder-7KSDKarolinska Sleep DiaryKSSKarolinska Sleepiness ScaleMEDASMediterranean Diet Adherence Screener tool (includes 14-item)PHQ-9Patient Health Questionaire-9POMSProfile of Mood StatesPSQIPittsburgh Sleep Quality IndexUWWBICUniversity of East Anglia Wellcome-Wolfson Brain Imaging CentreVASVisual Analogue Scale

#### Primary outcomes

##### Mood and anxiety

Mood and anxiety levels are monitored using two scales. The primary outcome measure is the Profile of Mood State score (POMS)^35^ with mood also scored using the Bond-Lader questionnaire.^36^ The former has 65 items measuring 6 elements of mood (namely anxiety, anger, confusion, depression, fatigue and vigour); while the latter has 16 items (alert, drowsy, calm, excited, strong, feeble, muzzy, clear-headed, well-coordinated, clumsy, lethargic, energetic, contented, discontented, troubled, tranquil, mentally slow, quick witted, tense, relaxed, attentive, dreamy, incompetent, proficient, happy, sad, antagonistic, amicable, interested, bored, withdrawn, gregarious) under four categories (1. mental sedation or intellectual impairment, 2. physical sedation or bodily impairment, 3. tranquillisation or calming effects and 4. other types of feelings or attitudes) or three mood factors (alertness, contentment and calmness). Both are commonly used in research including three of the four studies included in our systematic review,^25^ allowing a direct comparison of our findings with the limited published literature. The primary outcomes are the ‘contentment’ domain from Bond-Lader and the anxiety domain from POMS.

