### Statistical methods: data collection, management and analysis

#### Sample size calculation

The sample size calculation was based on data from a previous cross-over trial of the effect of MDP adherence in a young healthy adult group.^67^ Assuming an error rate of 0.05 and 90% power, we would require 15 and 20 participants to complete each arm for the primary outcome, which is the contentment, a mood domain from the Bond-Lader scale (9.6 unit expected difference, SD 10.3). To account for up to 20% dropout between random allocation to treatment sequence and study completion, we recruited 25 individuals.

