#### Analysis

The main aim of the trial is to test if mood and anxiety can be improved over 5 days of intervention. The primary outcome analysis will use two-way repeated measures analysis with paired analysis taking mean change-scores.

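### The article defines the primary outcome in three incompatible ways and fixes its time point only loosely, so it does not show which result counts as success

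*Protocol article*

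**What the plan says.** All of the following is in the protocol article.

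- Mood and anxiety, opening lines: "The primary outcome measure is the Profile of Mood State score (POMS"). Bond-Lader is introduced as an additional way of scoring mood.
- Mood and anxiety, last sentence: "The primary outcomes are the ‘contentment’ domain from Bond-Lader and the anxiety domain from POMS".
- Sample size calculation: the trial is sized for "the primary outcome, which is the contentment, a mood domain from the Bond-Lader scale", with an expected difference of 9.6, an SD of 10.3, an error rate of 0.05 and 90% power.
- Abstract, Methods and analysis: "The co-primary outcomes are mood and anxiety".

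On timing, the abstract's aim is to see whether the Mediterranean diet "improves mood, cognition and anxiety symptoms, postprandially, at 24-hour and after 5 days". The end of the Introduction repeats that span, and the Discussion describes the primary endpoint as running from postprandial to 5 days. Table 4 schedules both mood scales at baseline, postprandially, at 24 hours and on day 6. The Analysis section is narrower: "The main aim of the trial is to test if mood and anxiety can be improved over 5 days of intervention". It then gives a two-way repeated-measures analysis with paired change scores as the primary analysis, without naming the deciding contrast.

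**The concern.** A reader needs to know which variable, at which time, decides the trial. Here one paragraph makes POMS primary and Bond-Lader additional, then takes one of its two primaries from Bond-Lader. The sample size section drops POMS altogether. If contentment shows no difference and POMS anxiety does, the trial has failed under the Sample size section and may have succeeded under the end of the Mood and anxiety paragraph. If the POMS score differs and contentment does not, the verdict turns on the opening of that paragraph.

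This matters more than usual in this trial. Both scales are self-reported, the Discussion acknowledges that participants know which diet they are on, and Study setting puts data collection at June to December 2023. With open-label, self-reported outcomes, an unambiguous primary definition is one of the main protections against selective claims.

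**Working it through.** **Step 1: compare the definitions.**

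| Place | Primary outcome | Number |
|---|---|---|
| Mood and anxiety, opening | POMS score | one |
| Mood and anxiety, close | Bond-Lader contentment and POMS anxiety | two |
| Sample size calculation | Bond-Lader contentment | one |
| Abstract, Methods | mood and anxiety, co-primary | two |

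The abstract's labels fit the second row: the Sample size section itself calls contentment a mood domain, and the POMS domain is anxiety. That leaves three incompatible definitions.

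**Step 2: reproduce the plan's own figure.** Inputs from the Sample size section: difference 9.6, SD 10.3, error rate 0.05, power 90%, dropout 20%. Sidedness is not stated, so two-sided is assumed. The SD is taken as that of the within-person difference.

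- Standardised difference: 9.6/10.3 = 0.932.
- Paired t-test, noncentral t: 14 completers give 89.6% power and 15 give 91.8%. The stated 15 reproduces (a one-sided test would give 12).
- Recruitment: 20/(1 − 0.20) = 25, as stated.
- The stated 20 does not follow from 9.6/10.3. It would need a standardised difference of about 0.77 to 0.78, and the article does not say what it belongs to.

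If 10.3 were instead a per-period SD, the requirement would run from 27 completers (between-period correlation 0) to 10 (correlation 0.7). Correlation 0.5 again gives 15.

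**Step 3: type I error under the decision rules a reader could apply.** For k independent tests at 0.05, where any one suffices, the error is 1 − 0.95^k. For correlated tests, paired t-tests with n = 20 were simulated 100,000 times with equal correlation. The article gives no correlations, so these are assumptions.

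| Rule | Independent | 0.5 | 0.7 | 0.9 |
|---|---|---|---|---|
| Either of two outcomes, day 6 only | 1 − 0.95² = 9.75% | 9.0% | 8.4% | 7.1% |
| Either outcome at any of three times | 1 − 0.95⁶ = 26.5% | 21.3% | 16.8% | 11.2% |
| Both outcomes, day 6 | 0.3% | 0.8% | 1.5% | 2.9% |

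The last row assumes no effect on either outcome. If one outcome has a real effect and the other has none, the error of a both-must-succeed rule can approach 5% but cannot exceed it. The middle row is hypothetical, since no part of the article states such a rule.

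**Step 4: price of a fixed rule for contentment, 20 completers.**

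- Alone, two-sided 0.05: power 97.7%.
- Two-sided 0.025, the stricter step of Holm with two tests: power 95.0%; 17 completers suffice for 90%.
- For comparison, six tests at 0.05/6 each: power 87.3%; 22 completers needed for 90%.

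The same check cannot be made for POMS anxiety, which has neither a difference nor an SD.

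**The case against.** The strongest reply has four parts.

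- The closing sentence of the Mood and anxiety paragraph names domain and scale, the abstract agrees with it, and sizing a trial on one of two primaries is not in itself a contradiction. The two sample sizes might even be one per primary. This is right as far as it goes, and it is why the count is three. It does not remove the sentence naming the POMS score or the singular in the Sample size section. The article does not say what the second sample size is for.
- The time lists in the aims also include cognition, which is secondary, so they are not a list of primary tests. Table 4 is only a schedule, and the Analysis section singles out the 5-day period. This largely stands: the primary time is indicated, though loosely. A change over 5 days could still include the intermediate measurements, and the Discussion attaches the primary endpoint to the whole span.
- A reader might infer a false-positive risk far above 5%, up to the six-test figure. The article does not support that. It plans one repeated-measures analysis, not six separate tests, and nowhere says that either outcome or any time suffices.
- A reader might also infer that multiplicity is unadjusted, or that the winning outcome can still be chosen after seeing the data. Both rest on silence. A condensed article may leave the error-rate procedure to an analysis plan that is not shown, and that plan may fix it.

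What remains is the contradiction about the primary outcome itself. An unseen plan cannot cure conflicting statements in this text.

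**Conclusion.** The concern holds as an internal contradiction: three definitions of the primary outcome, a loosely indicated time point, and so no way to tell from the article which result is a success. The false-positive consequence is conditional. It is about 7% to 10% if either outcome at day 6 may be claimed at 0.05, and at most 5% if both are required. The wider range of about 11% to 27% belongs to a six-test rule that the article does not state, and should not be presented as the trial's error rate. These figures rest on two-sided tests, 20 completers and assumed correlations between 0 and 0.9. The contentment power figures also take 10.3 as the SD of the within-person difference, the reading that reproduces the stated 15.

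**What to change.** Bring the abstract, Mood and anxiety, Sample size calculation and Analysis sections to one definition, using the article's most specific statement: Bond-Lader contentment and the POMS anxiety domain, each compared between diets at day 6, the end of the 5 days.

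- Remove or correct the sentence that makes the POMS score the primary measure, and the singular primary outcome in the Sample size section.
- State the decision rule: either both outcomes must succeed, each at 0.05, or either suffices, with Holm at a family-wise two-sided 0.05. Both control the error; the choice is the sponsor's.
- Label the postprandial and 24-hour contrasts secondary.

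The cost is wording, settled before the analysis is run. The earlier time points could then no longer carry the main claim. Under Holm, contentment loses little (97.7% to no less than 95.0% with 20 completers). The cost for POMS anxiety, and the joint power if both must succeed, is unknown until a difference and SD are given for that domain.
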